### Criteria for dropout

The criteria for discontinuing the assigned interventions are:The patient's willingness to discontinue participation in the study.Worsening prognosis that precludes continuation.The presence of events during the sessions jeopardizes the patient's safety.Absence from training sessions, in the case of the experimental group for unjustified reasons (compliance below 60%).

### Study outcomes

Anthropometric and demographic variables will be collected for descriptive analysis only in the first evaluation, including age, gender, weight, height, and body mass index. Participants must complete different questionnaires that will be conducted at each measurement time. The summary of the outcome variables can be found in Additional file 3.

#### Primary outcome measures

As primary variables, one has been chosen for each of the three domains that are going to be evaluated.

##### Biomechanical biomarkers

The kinematic parameters during the activity are derived by using inertial measurement units (IMU). IMUs have been shown to have good psychometric properties to estimate kinematic parameters during the performance of functional tests. Kinematic parameters have been seen as objective parameters of functional capacity. It has been shown to have high specificity and sensitivity for tests such as the 6MWT in patients with HF.

##### Physiological biomarkers

Peak oxygen uptake (VO_2_peak), in maximal exercise tests, coincides with maximal oxygen consumption (VO_2_max). It is the most objective parameter of functional capacity and a gold standard indicator of maximal cardiorespiratory fitness. It is the maximum O_2_ extracted from inhaled air during pulmonary ventilation. It is usually expressed in milliliters per minute (ml/min) or milliliters per kilogram per minute(ml/kg/min). It reflects the severity of the disease in patients with HF [39, 40] and is a significant predictor of mortality in HF patients [41].

##### Imaging biomarkers

Assessment of ultrasonic body composition parameters can be performed using ultrasonography (US). This technique is reliable and valid for evaluating the number of pennate muscles in older adults, such as the quadriceps femoris (QF) muscle. US has shown reasonable validity in estimating muscle mass compared to MRI and CT. US could have the potential for use in clinical practice for the detection of sarcopenia and to assess body composition or muscle architecture.

#### Secondary outcome measures

For the secondary variables, we have chosen to describe the instruments used to capture the different variables. The variables assigned to each instrument are well-detailed in Additional file 3.

### Objective outcome variables

#### Physiological biomarkers

##### Electrical impedance vector analysis (BIVA)

As a measure of body composition, electrical bioimpedance vector analysis (BIVA) has been validated. It has recently been shown to provide information on the overall assessment, management, and prognostic evaluation of HF patients [42, 43]. All measurements derived from BIVA are characterised by excellent test–retest reliability [44]. The BIO 101 BIVA®PRO bioimpedance device (BIA101 Akern, 50,065 Pontassieve FI, Italy) will be used.

##### Respiratory function tests (RFT)

To measure the patient's respiratory volumes and flows, a spirometry device (Spiro USB, Micro Medical, Kent, UK) [45] and a respiratory pressure meter (MicroRPM, Micromedical, Kent, UK) [46] will be used to test the lung function [46–48]. The repeatability of spirometry measurements [49] and the reliability of the MicroRPM device for MIP and MEP [50] variables have been reported. The recommendations of the ARTP statement on pulmonary function tests in 2020 will be followed [51].

##### High-density electromyography (HD-sEMG)

The high-density electromyography (HD-sEMG) device will be used in conjunction with the S-type load cell (Biometrics Ltd., Newport, UK) to measure the electrical activity of the tibialis anterior (TA) muscle and generate force output. It is a reliable method for assessing the characteristics of the motor unit in different populations and locations [52–55]. The signal produced will be recorded using the external analog-to-digital signal converter Sessantaquattro (64-channel EMG amplifier; OT Bioelettronica, Turin, Italy), and will be processed using OT Biolab + software (v.1.2.1, OT Bioelettronica, Turin, Italy) [56].

##### Functional and dynamometric tests (FUN test)

Patients will undergo the Short Physical Performance Battery (SPPB) [57–59], Timed Up and Go Test (TUG) [57, 60], and Six-Minute Walk Test (6-MWT) [58, 59, 61, 62]. A digital hand dynamometer will assess isometric quadriceps extension strength (J Tech Medical, Powertrack II Commander, Salt Lake City, UT) [63]. Grip strength will be evaluated using the Jamar Hydraulic, model SH5001 (Lafayette Instrument, Lafayette, USA). Manual dynamometry has proven to be a valid and reliable instrument to measure isometric strength in different populations and locations [64, 65].

##### Cardiopulmonary Exercise Tests (CPET)

Cardiopulmonary exercise testing (CET) will be performed using a portable Cortex Metamax 3B (MM3B) [66] automated gas analysis system[ref]. Primarily to obtain VO_2_peak, secondary to collect variables derived from breath-by-breath respiratory gas analysis. The self-limited ramped exercise protocol on an ergometer bike is generally well tolerated by patients with HF [67]. The feasibility and safety of the ramped exercise protocol have been demonstrated [68].

##### Blood biomarkers

The relevant physician will extract biomarkers in the blood through blood analysis (blood, plasma, and serum). The central blood values of interest in the HF population will be requested.

#### Biomechanical biomarkers

During functional tests, biomechanical parameters will be assessed using the inertial measurement unit of the Shimmer3 [69] and the structured light-based depth camera manufactured by Xbox360, the Kinect 2.0 sensor [35, 70, 71].

#### Imaging biomarkers

Standard two-dimensional resting echocardiography (ultrasound) will be used to obtain cardiac imaging variables. Simpson's biplane method will be used in an apical four-chamber view to estimate LVEF (%) [29, 31]. A B-mode ultrasound (SonoSite 180 Plus, SonoSite Japan, Tokyo, Japan) and linear transducer (5–10 MHz) [72] will be used to collect skeletal and pulmonary imaging variables.

### Self-reported outcome variables

The abbreviated comprehensive assessment scale (aCGA) [73, 74], the SARC-F questionnaire [75, 76], the Kansas City questionnaire (KCCQ) [77], and the Mini Nutritional Assessment survey (MNA®) [78] are validated and, will be used to obtain the outcome variables self-reported.

### Exploratory outcomes

During the sessions, the total exercise time and the exercise intensity reached by the patients during the sessions will be collected. In addition, adverse events during the exercise program will be compiled.

The cost of the CR per session will be estimated from the material required, the clinician's time, and the indirect costs.

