## Methods

### Trial design

This study protocol followed the SPIRIT 2013 Recommendations [36] during its development. More details are shown in Additional file 1. The present study shows the proposed two-arm crossover RCT comparing an exercise-based CR programme with education in patients with HF. Patients will be randomised into two groups by simple randomisation using a random number generator on the computer. The study design is shown in Fig. 1. The RCT is based on work within the Biomedical Research Institute of Malaga (IBIMA) between the Internal Medicine Unit and the Cardiology Unit of the Regional University Hospital of Malaga (HRUM), together with the support of the University of Malaga (Malaga, Spain). This project has been submitted to the Malaga Provincial Ethics Committee (2198-N-22).

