## Interventions

Both the Education and CR interventions will take place in the internal medicine unit of the HRUM. Medical and nursing care will be available during Education and CR sessions to ensure the safety of participants Study collaborators will be instructed to record any incidents related to possible adverse events that may be associated with the interventions.

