### Experimental group: CR program

The CR programme will consist of aerobic and strength exercise sessions. Exercises will be individualised after assessment of short (strength exercise) and long (aerobic exercise) efforts. They will be performed two days a week and at least 48 h between sessions. Progression will consider a clinical criterion, determined by the absence of HF symptoms at the current intensity, and a time criterion in which, as long as the clinical criterion is met, the intensity will be increased every two to three weeks. The progression in aerobic training intensity is established based on Skinner's three-phase model [38] and the recommendations of current European cardiac rehabilitation guidelines [29]. The structure of the standard session, the criteria for progression in both aerobic and strength training, the phases of training, the periodisation of the programme, and the monitoring variables in the session can be found in detail in Additional file 2.

In addition, embedded in the exercise intervention, education on healthy lifestyle habits will be needed. A series of competencies in healthy lifestyle habits relevant to the population with HF will be established, which will be evaluated using a questionnaire with an evaluation rubric format for each of the competencies. The competencies will be evaluated during the training sessions in an informal way. Depending on the results obtained, they will be reinforced by strengthening unconsolidated skills using specific educational material.

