### Control group: Education

The control group will receive personalized educational embedded in the program for twelve weeks on HF complications, functional decline, and healthy lifestyle habits. The format of the sessions will be in the form of face-to-face or online master classes, depending on the availability of the participants, in which the active participation of both volunteers and their relatives/caregivers will be encouraged.

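### The two statements on adverse events differ in scope, and neither gives a like-for-like count in the rehabilitation and education conditions

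*Protocol article*

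**What the plan says.** The trial is a "two-arm crossover RCT comparing an exercise-based CR programme with education in patients with HF". Two places in the article deal with adverse events.

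- **Exploratory outcomes.** After exercise time and intensity, the section states that "adverse events during the exercise program will be compiled". This is the only place where adverse events appear as an outcome. No corresponding outcome is named for Education.
- **Interventions.** The opening paragraph covers both conditions: "Medical and nursing care will be available during Education and CR sessions to ensure the safety of participants". It continues: "Study collaborators will be instructed to record any incidents related to possible adverse events that may be associated with the interventions".

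Three other sections bear on how events come to notice. Exercise sessions are twice weekly ("They will be performed two days a week and at least 48 h between sessions", Experimental group: CR program). The Abstract gives one education session a week for 12 weeks, and the Control group section allows these to be "face-to-face or online master classes". The Criteria for dropout list reasons for ending the assigned intervention, among them "Worsening prognosis that precludes continuation".

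**The concern.** Participants are aged about 70 or more, with heart failure in NYHA class 2 or 3. Admissions, falls and decompensation will occur in such patients whether or not they exercise. To tell background events from harm caused by the programme, events must be counted in the same way in both conditions over the same weeks. The randomised first period allows exactly that comparison.

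The stated rules do not secure it. One ties the outcome to exercise. The other makes perceived association the gate for recording, and that perception depends on which intervention the patient is receiving. Background events could therefore be charged to the programme because the matching events under Education were never written down.

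**Working it through.** The article gives no figure for adverse events, so there is none to reproduce. The point rests on setting the two statements side by side.

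| | Exploratory outcomes | Interventions |
|---|---|---|
| Conditions covered | Exercise programme | Education and exercise |
| Condition for recording | None stated | Possible association with an intervention |
| Status | Defined outcome | Instruction to staff |

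**1. Scope.** The first column excludes Education and the second includes it. A team following both would record Education incidents that belong to no defined outcome.

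**2. Effect of the filter.** For one condition, write recorded risk = r × d × a. Here r is the true risk, d the chance that an event comes to notice, and a the chance that it is thought possibly associated with the intervention. Then

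recorded ratio (exercise/Education) = (r_E/r_C) × (d_E/d_C) × (a_E/a_C).

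This equals the true ratio only if the last two factors multiply to 1. Under the Interventions rule, a_E is likely to exceed a_C, because a fall or decompensation is more readily linked to physical training than to a class. Under the Exploratory outcomes rule there is no Education term at all.

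**3. Contact.** Exercise: 2 × 12 = 24 sessions. Education: 1 × 12 = 12 sessions, some possibly online. If detection is proportional to contact (an assumption; the article does not say how incidents come to notice), then d_E/d_C = 24/12 = 2. With equal true risks and equal a, the recorded ratio would be 2.

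**4. Illustration.** Assume a background 12-week risk of 5% to 15% (not in the article) and the planned 63 patients per group. Expected events per group are 63 × 0.05 = 3.2 to 63 × 0.15 = 9.5. With full detection under exercise and half under Education, the recorded counts would be about 3.2 against 1.6, or 9.5 against 4.7, with no true difference.

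**5. What the numbers can support.** With 63 per group and two-sided 0.05 (normal approximation), power is 46% for 5% against 15%, and 35% for 10% against 20%. An exercise-only count with no events gives a one-sided 95% upper bound of 1 − 0.05^(1/63) = 4.6%, or 1 − 0.05^(1/126) = 2.3% if all 126 patients exercise after the crossover. That bounds the risk while exercising but says nothing about the excess over Education.

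**The case against.** A reader might infer that events are collected only under exercise, so that the trial yields a one-armed count and cannot show whether rehabilitation adds harm. The article does not support that reading, for four reasons.

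- The Interventions section plans incident recording in both conditions.
- In a crossover both sequences are due to exercise, so even the exercise-only outcome draws on both randomised groups.
- Exercise time and intensity are tied to sessions, whereas adverse events are tied to the programme. The programme wording can include the days between sessions.
- The Criteria for dropout do not say that event collection ends when the intervention does.

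It is also fair to say that the recording threshold is low (possible events that may be associated), that adverse events are exploratory, that the stated aim is efficacy on biomarkers, and that observation windows and questionnaires are usually left to the full protocol. That document and the additional files are not shown.

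All of this stands against the stronger reading. It does not remove the mismatch: the article states two scopes, and the broader one filters on suspected association. These are stated rules, not detail left for later, and a fuller document would not make the two sections agree.

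**Conclusion.** The concern holds in a limited form. The two sections disagree on scope, and neither as written gives a count with the same scope and filter in both conditions. The disagreement is plain from the text and needs no assumption. The direction of the filter's effect, towards fewer recorded events under Education, is a judgement about how staff would apply it. The twofold detection ratio rests on recording following session contact, and the event counts rest on an assumed 5% to 15% background risk; both are illustrations only. The trial is not powered for harm, so what is at stake is a fair descriptive comparison and not a test. This is an inexpensive improvement that should be made.

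**What to change.** Reconcile the Interventions and Exploratory outcomes sections under one rule:

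- Record all adverse and serious adverse events, including heart failure admissions, falls and deaths, from randomisation to week 24, in both groups and both periods, whether or not thought related.
- Include patients who stop the intervention.
- Ask the same questions of everyone at the existing 12- and 24-week visits, so that recording does not depend on session attendance.
- Judge relatedness after recording, not as a condition for it.
- Tabulate by randomised group and period, with weeks 0–12 as the main descriptive comparison.

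The cost is one form page, a few minutes at visits already planned, and a longer list of mostly unrelated events.

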### Data management

The data will be recorded and stored in database files on a password-protected flash drive. No identifying information is registered in the database, but an identification number is attributed to each patient. This number is associated with the patient's medical record number in a separate table accessible only to FUNNEL + researchers on a corporate computer. All patient information will be pseudonymised and only researchers will have access to the identification data.

### Blinding

The researchers conducting the assessments and data analysis will be blinded so that they do not know to which group each patient belongs. Blinding the subjects is unfeasible because of this type of intervention.

### Sample size calculation

The sample size was calculated using G Power 3.1.9.2 software (University of Düsseldorf, Germany). Based on an expected difference in VO_2_max increase of 3.0/ml/kg/min in the intervention group and 0.6 ml/kg/min in the control group (based on the result of the EUCaRE Study, Prescott et al. 2020 PMID 32102550 [48]). Assuming a statistical power of 80% and an alpha error of 0.05, the required sample size is 55 patients per arm and carries a loss rate of 15%, and this would make a total of 126 (63 per arm).

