### Statistical analysis

Data sets will be processed using the Statistical Package for the Social Sciences (SPSS) for Windows (version 19.0, SPSS Inc., Chicago, IL, USA). Qualitative variables will be described by absolute and relative frequency (percentage). Quantitative variables shall be presented by the mean and standard deviation if the data follow a normal distribution or by the maximum, minimum, and three quartiles if the data do not follow such a distribution. The Shapiro–Wilk test will be used to analyse the normal distribution of the data (*p* > 0.05). The difference in means between the two groups will be obtained using Pearson's Chi-square test (× 2) for qualitative variables. To express the differences in means in the quantitative variables between the two groups, the bivariate analysis will be used using the parametric Student's t-test for independent samples in the case of normal data distribution, or the non-parametric Mann–Whitney U test, if there is no normal distribution of the data. The degree of statistical significance shall be set at a *p*-value < 0.05. 95% confidence intervals (CI) will be calculated for the mean differences between the study groups.

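### The 15% loss allowance is added as 55 × 1.15, so 126 patients leave about 107 evaluable rather than 110; the effect on power is about one percentage point or less

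*Protocol article*

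**What the plan says.** The section on sample size calculation in the protocol article plans for an "expected difference in VO_2_max increase of 3.0/ml/kg/min in the intervention group and 0.6 ml/kg/min in the control group", a between-group difference of 3.0 − 0.6 = 2.4 ml/kg/min. The error rates are given as "Assuming a statistical power of 80% and an alpha error of 0.05". From these the section concludes that "the required sample size is 55 patients per arm and carries a loss rate of 15%, and this would make a total of 126", which it splits as 63 per arm. It does not show how 15% turns 55 into 63.

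The section on statistical analysis compares the two groups with an independent-samples t-test when the data are normally distributed, sets significance at p < 0.05, and adds that "95% confidence intervals (CI) will be calculated for the mean differences between the study groups".

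**The concern.** A loss allowance exists so that the required number is still there after the losses. If a fraction *d* of those randomised is lost, the number to randomise is the required number divided by (1 − *d*). Multiplying by (1 + *d*) gives too few, because the loss falls on the enlarged sample and not on the original 55. The protocol's 63 per arm looks like the product of that multiplication, with the fraction then rounded down. If so, 55 per arm, 15% loss and 126 enrolled cannot all be true together, and the 80% power attached to 55 per arm does not strictly carry over to a trial of 126 with 15% loss. What is at stake is whether one planning statement is correct, and whether the error costs enough power to matter.

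**Working it through.** **Inputs, all from the sample size section unless marked.** Required evaluable number: 55 per arm (110 in total). Loss: 15%. Enrolment: 126 (63 per arm). Difference: 2.4 ml/kg/min. Power 80%, alpha 0.05. Test: independent-samples t-test (statistical analysis section). *Assumptions:* the test is two-sided, and the standard deviation is the one implied by 55 per arm, since the article prints no value.

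**1. Reproducing the protocol's figure.**
- 55 × 1.15 = 63.25, rounded down to 63 per arm.
- 110 × 1.15 = 126.5, stated as 126.

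The figure is reproduced by multiplication and rounding down. Division does not give it: 55 / 0.85 = 64.7.

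**2. What remains after 15% loss.**
- 63 × 0.85 = 53.55 per arm.
- 126 × 0.85 = 107.1 in total, against 110 required.
- Rounding up instead would not repair it: 64 × 0.85 = 54.4, still below 55.

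**3. What 126 can absorb.** The margin is 63 − 55 = 8 per arm, so the tolerable loss is 8 / 63 = 12.7%.

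**4. What 15% loss would correspond to.** 55 / 0.85 = 64.7, so 65 per arm and 130 in total. Check: 65 × 0.85 = 55.25. The difference from the stated figure is 2 per arm, 4 in total.

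**5. Effect on power.** For *n* per arm, the two-sample t statistic follows a noncentral t distribution with 2*n* − 2 degrees of freedom and noncentrality (2.4 / SD) × √(*n* / 2). Power is the probability that it falls outside the two-sided 5% critical values.

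If 55 is the smallest whole number reaching 80%, then power at 55 is at least 80% and power at 54 is below 80%. Solving at the two limits gives an SD between 4.41 (standardised difference 0.544) and 4.45 (standardised difference 0.539).

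| Evaluable per arm | Power, SD 4.45 | Power, SD 4.41 |
|---|---|---|
| 55 | 80.0% | 80.7% |
| 54 | 79.3% | 80.0% |
| 53.55 (expected at 15% loss) | 78.9% | 79.7% |
| 53 | 78.5% | 79.3% |

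For example, at 53.55 per arm and SD 4.45 the noncentrality is 0.539 × √26.775 = 2.79, compared with 0.539 × √27.5 = 2.83 at 55 per arm.

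At the expected 53.55 per arm, the shortfall from 80% is 80 − 79.7 = 0.3 to 80 − 78.9 = 1.1 points.

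**The case against.** The strongest reply is that this is trivial. The correction is 2 patients per arm, the 15% is itself a planning guess, and 126 tolerates 12.7%, only 2.3 points less. At 54 per arm, power can still be 80.0%. No part of the design, analysis or interpretation would change. All of that stands, and it sets the weight of the point. It does not make the sentence correct: the article prints the required number, the loss rate and the total, and they disagree.

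A second reply is that a journal article condenses a fuller protocol. That disposes of any complaint that the SD and the sidedness of the test are not printed, since they may well be given elsewhere. It does not cover the loss allowance, which is a figure stated wrongly and not a detail left out.

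A reader might go further and infer that the trial is materially underpowered. One could suppose, for instance, that 55 came from a one-sided calculation with a larger SD, so that two-sided power would be well below 80%. The document does not support this. Nothing in it says the calculation was one-sided, and p < 0.05 reported with 95% confidence intervals is the usual two-sided convention. Power figures obtained by trying other SDs would reflect the SD chosen and not this error.

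**Conclusion.** Wrong as written, but minor. The arithmetic is certain and uses only the article's own figures: with 15% loss, 126 enrolled leaves about 107 evaluable, not 110, and 55 per arm is retained only up to 12.7% loss.

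The size in terms of power rests on two assumptions: a two-sided t-test, and an SD at the value implied by 55 being the smallest sufficient number. On those terms expected power is about 79% to 80%. It would be too strong to say that the planned power is missed in any way that matters; the documents support only that it falls about one point or less below the stated 80%.

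**What to change.** Keep 126 and restate the closing sentence of the sample size section in one of two equivalent ways:

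- 126 patients (63 per arm) will be randomised; after 15% loss about 107 will be evaluable, giving power of about 79%; or
- 126 patients (63 per arm) will be randomised, which retains 55 per arm for loss of up to 12.7%.

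For reference, retaining 55 per arm after 15% loss would correspond to 65 per arm (130 in total).

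The cost is an edit to one sentence, in which one stated figure becomes slightly less favourable. With 126 kept, no further patients are needed and nothing else in the plan changes.
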